**Frailty**
Frailty will be assessed before and after each research period according to the most often used frailty scale in PD [4] frailty phenotype (FP) status [114], in which 5 criteria have to be assessed: (1) unintentional weight loss >5 kg the last year, (2) weakness (HSG for men: <27 kg and women: <16 kg), (3) slow walking speed (10-m usual walking speed test ≤0.8 m/s), (4) exhaustion (PFS-16 total score ≥3, which indicates moderate to severe fatigue), and low levels of physical activity (a total score <600 MET/min/week^-1^ indicates inactivity in the Greek version of International Physical Activity Questionnaire-Short Form [115]). The FP score ranges from 0 to 5 (1 point for each criterion; 0: best score to 5: worst score), and defines as frail an individual with a score of ≥3, as prefrail an individual with a score of 1 to 2, and as nonfrail or robust an individual with a score of 0.
**Balance**
Balance will be assessed before and after each research period by the Greek version [116] of Berg Balance Scale [117], which is a 14-item validated in PD [118] scale with a minimum score of 0, and a maximum score of 56, while lower scores indicate worse balance (0-20: high fall risk, 21-40: medium fall risk, and 41-56: low fall risk).
**Cognitive functions**
Cognition will be assessed before and after each research period by the Greek version [119,120] of Montreal Cognitive Assessment (MoCA) [121], which is a 0- to 30-point scale with lower scores indicating cognitive impairment.
**Movement and nonmovement PD symptoms**
Movement and nonmovement PD symptoms will be assessed before and after each research period by the Greek version of Movement Disorder Society–sponsored revision of the Unified Parkinson’s Disease Rating Scale (MDS-UPDRS) [122], which is a 4 parts scale. Part I assesses nonmotor experiences of daily living (13 items, score range: 0-52), part II assesses motor experiences of daily living (13 items, score ranges: 0-52), part III assesses motor signs (33 items, score ranges: 0-132), and part IV assesses motor complications, namely dyskinesias and motor fluctuations (6 items, score ranges: 0-24). Each item score ranges from 0 (normal) to 4 (severe), and higher scores indicate a greater impact of PD signs.
**BMI**
BMI will be assessed before and after each research period by the score from the equation kg/m^2^, with <18,5 indicating underweight, 18.5 to 24.9 indicating normal weight, 25 to 29.9 indicating overweight, and ≥30 indicating obesity (3 obesity subcategories exist: Class I scores of 30-34, Class II scores of 35-39, and Class III scores of ≥40) [123].

### Sample Size

A prospective, nonrandomized, uncontrolled, open-label pilot study has already been conducted in a Greek population of 16 patients with early- to midstage PD, showing that in-person DfPD is safe and feasible, and can improve QoL, as well as several movement and nonmovement PD symptoms [45]. According to the results of the above pilot clinical trial for our primary outcome (QoL), the Cohen equations for sample size calculation [124], and considering the power of the study equal to 80% and the level of statistical significance of the controls equal to the conventional limit of statistical significance (α=.05), a power analysis was applied with the a priori formula for the *F* test statistical control through analysis of variance with repeated measures using G*Power software (version 3.1) [125].

Taking in consideration that the number of experimental groups will be 3, the number of repeated measurements for each participant will be 6, and the average correlation coefficient between repeated measurements will be 0.64, it was estimated that for this study, which has a 1:1:1:1:1:1 distribution ratio of participants to the groups, at least 6 participants are required in each group (18 in total). On the basis of the equations that adjust the sample size to the expected dropout rate [126], which is expected to be up to the 15% acceptable value, based on the Physiotherapy Evidence Database Scale [99], the minimum sample size required to achieve the study’s primary end point (QoL) is 21 participants.

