### Statistical Analysis

The primary analysis will evaluate the between group differences in total score of the Greek version of Parkinson’s Disease Questionnaire-8 after each research period. Mean (SD) or summary statistics appropriate to the distribution of the QoL total score will be reported by study group (in-person DfPD vs online DfPD vs control). Study groups will be compared in terms of QoL using mixed model repeated measures considering the correlated data from the same patient [128]. Mixed model repeated measures are robust in small sample size studies; thus, a decreased risk of type II errors occurs [129]. For all secondary end points, summary statistics will be tabulated by study group, and study groups will be compared with a statistical method appropriate to the type of the end point (eg, continuous and categorical end point). Bonferroni correction will be used to account for multiple comparisons of secondary outcomes.

A secondary analysis of the primary end point will adjust for those prerandomization variables which might reasonably be expected to be predictive of favorable QoL total score. Any deviations from the protocol will be recorded and agreed by the investigators. Missing data will not be imputed neither for primary nor secondary analyses, and no interim analyses will be conducted in this study. All the *P* values are 2-sided at an α level of .05. Analyses will be conducted with SPSS (version 20.0; IBM Corp) and R (version 4.4.1; R Foundation for Statistical Computing).

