## Results

The study is a 3-arm crossover and open-label randomized controlled trial (in-person DfPD vs online DfPD vs control), and was partially funded in September 2023. The first participant was enrolled in April 2023. The trial is currently ongoing, and will conclude in September 2024. A total of 47 patients were enrolled during the recruitment period, of whom 7 have been excluded (Figure 1). A total of 40 patients were randomized equally to the study’s 6 sequences to undergo sixteen 60-minute culturally tailored DfPD classes both in-person and online during a 10-month experimental period following a patient-centered approach. The data analyst will analyze all the data after the final participant exists the study. We expect that by the second quarter of 2025, the study’s results will have been published.

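### The sample size is calculated for three separate groups of 6 patients, not for the six-sequence crossover, so the stated 80% power at 18 does not carry over to the primary comparison

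*Protocol article*

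**What the plan says.** All of this is in the protocol article.

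- **Sample Size, method.** A repeated-measures ANOVA F test in G*Power, "considering the power of the study equal to 80" percent, at the "conventional limit of statistical significance (α=.05"). The option used (between, within or interaction) is not named.
- **Sample Size, effect.** The source is given ("According to the results of the above pilot clinical trial for our primary outcome (QoL")), but no effect size or SD. The pilot was uncontrolled, had 16 patients and tested in-person classes only.
- **Sample Size, layout.** "the number of experimental groups will be 3, the number of repeated measurements for each participant will be 6", with an average correlation of 0.64.
- **Sample Size, result.** The study is one "which has a 1:1:1:1:1:1 distribution ratio of participants to the groups, at least 6 participants are required in each group (18 in total"). With dropout of up to 15%, the minimum for the "primary end point (QoL) is 21 participants".
- **Study Design (Table 1) and Assignment of Interventions: Allocation.** Each patient is randomised to one of six sequences and passes through in-person dance, online dance and control.
- **Statistical Analysis.** Conditions are compared on the PDQ-8 total after each period by a mixed model that allows for repeated data from one patient. P "values are 2-sided at an α level of .05".
- **Primary Outcomes.** The primary outcome is the change in the PDQ-8 total over each period.
- **Results.** "A total of 40 patients were randomized equally" to the six sequences.

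**The concern.** The calculation multiplies 3 groups by 6 patients to get 18, which makes sense only if each group holds different patients. In this crossover nobody belongs to a single group. The six measurements are three before-and-after pairs, each under a different condition. The same sentence also attaches a six-way ratio to three groups: six groups of 6 would be 36, and 18 spread over six sequences is 3 in each. Both descriptions cannot be right.

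At stake is what a reader may conclude from the results. The article presents the comparison of in-person with online delivery as new. An uncontrolled in-person pilot cannot supply an assumed difference for that contrast, and no power is stated for it. If the contrast is not significant, a reader who relies on the printed 80% may take that as evidence of similarity, although the figure was never calculated for it.

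**Working it through.** **1. Reproducing the plan's 18.** Inputs from Sample Size: k = 3 groups, m = 6 measurements, ρ = 0.64, α = .05, power 80%. The effect size f is missing, so 18 cannot be derived from the printed inputs. Working backwards with G*Power's noncentral F formulas, in steps of 3 patients, 18 is the minimum for these ranges of f:

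| Option | λ | df | f giving 18 |
|---|---|---|---|
| Group-by-time interaction | f²Nm/(1−ρ) | 10, 5(N−3) | about 0.247 to 0.274 |
| Within factor (time) | f²Nm/(1−ρ) | 5, 5(N−3) | about 0.214 to 0.237 |
| Between factor (group) | f²Nm/(1+5ρ) | 2, N−3 | about 0.68 to 0.76 |

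Example for the interaction at f = 0.25: λ = 0.0625 × 18 × 6/0.36 = 18.75 with df 10 and 75, power 81%. At N = 15, power is 70%. In all three options the groups hold different patients. None is a within-patient comparison of three treatments.

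**2. The crossover treatment test.** Each patient contributes one score per condition.

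- End-of-period scores: λ = f² × N × 3/(1−ρ), df 2 and 2(N−1)−2, where the last 2 df go to periods.
- Change scores: if all scores are equally correlated, the error variance doubles and λ halves.

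Assumed f = 0.25 on the three treatment means; ρ = 0.64 as stated. At N = 18 on end-of-period scores, λ = 0.0625 × 18 × 3/0.36 = 9.375; on change scores it is 4.69. The denominator df is 32 in both.

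| Patients analysed | End-of-period score | Change score |
|---|---|---|
| 18 | 75% | 44% |
| 21 | 82% | 51% |
| 34 (40 × 0.85) | 97% | 74% |
| 40 | 98.5% | 82% |

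For f from 0.20 to 0.30, 80% power needs 31 down to 15 completers on end-of-period scores, and 60 down to 28 on change scores.

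**3. Pairwise contrasts.** In units of the between-patient SD of a single score, with ρ = 0.64:

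- Within-patient SD: √(1−0.64) = 0.60.
- SD of the difference between two conditions, end-of-period scores: √(2 × 0.36) = 0.85.
- The same for change scores, equal correlation: √(4 × 0.36) = 1.20.

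The difference detectable with 80% power at two-sided .05 is roughly (t for .975 + t for .80) × SD of the difference/√N:

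- N = 34: (2.03 + 0.85) × 0.849/5.83 = 0.42 SD on end-of-period scores; 2.88 × 1.20/5.83 = 0.59 SD on change scores.
- N = 40: (2.02 + 0.85) × 0.849/6.32 = 0.39 SD; 2.87 × 1.20/6.32 = 0.54 SD.

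**4. Dropout step.** 18/0.85 = 21.18, which rounds up to 22, while 18 × 1.15 = 20.7 rounds up to 21. In whole patients, at most 15% of 21 is 3, which leaves 18.

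**The case against.** The strongest reply is that the consequence is small. The section states a minimum, 40 were randomised, 40 also appears as the recruitment target under the feasibility outcomes, and recruitment is closed. Nothing shows that the trial is underpowered. That stands. It does not rescue the printed figure, because 40 is a recruitment target and is not linked to any power calculation.

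A second reply is that a condensed article may leave the effect size to the pilot report it cites. That also stands: the missing value is a request for reporting. But the inputs that are printed contradict the printed design, and that is a misstatement, not an omission.

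A reader might infer more than the document supports:

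- *That 18 arises only from a group-by-time interaction.* It does not. All three options give 18 for some f, and the option is not named.
- *That the analysis never performs such a test.* Statistical Analysis lists no fixed effects, and comparing changes between conditions is itself a condition-by-time contrast. The fair criticism is that the calculation treats condition as a between-patient factor.
- *That 40 is certainly enough, or certainly too few.* At the assumed f, 34 completers give 97% or 74% power, depending on the score.
- *That 21 is an error.* Strict rounding gives 22, but the gap is one patient and 21 less 3 dropouts leaves 18. It is at most a rounding remark.

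**Conclusion.** The point holds in this form: the 80% power at 18 (21 with dropout) was calculated for three groups of different patients and does not transfer to the within-patient primary comparison. The six-way ratio beside three groups of 6 is a contradiction within one sentence and needs no assumption to see. The in-person versus online contrast and the 40 randomised have no power statement.

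The size of the discrepancy is illustrative only. It rests on an assumed f of 0.25, on the stated 0.64 applying equally to all pairs of scores, and on complete data from those analysed. If scores within a period correlate more strongly than scores from different periods, change scores lose less than shown. An f for a group-by-time interaction is also not the same quantity as an f for a crossover treatment effect, so the 81% and the 75% at 18 should not be read as a like-for-like loss. What is firm is that the answer depends heavily on whether the end-of-period score or the change score is analysed, and the document points to both.

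**What to change.** Replace the calculation in Sample Size by one for the three-treatment, six-sequence crossover:

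1. Name the PDQ-8 score the primary model analyses (end-of-period or change), in agreement with Primary Outcomes and Statistical Analysis.
2. State the PDQ-8 difference assumed for dance versus control and the SD behind it. With ρ = 0.64, use a within-patient SD of 0.60 SD, or an SD of the difference between conditions of 0.85 SD (end-of-period) or 1.20 SD (change), and say which of these enters the formula.
3. Withdraw the claim of 80% power at 18, or restate it for that test, and remove the conflict between three groups and a six-way ratio.
4. Say that 40 were randomised, and give the difference detectable with 80% power for each pairwise contrast, including in-person versus online, at 40 and at 34 completers. Under the assumptions above, 34 gives about 0.42 SD (end-of-period) or 0.59 SD (change); convert these to PDQ-8 points.
5. If a dropout-inflated minimum is kept, show the formula and rounding.

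The cost is one rewritten paragraph. Because recruitment is closed, the new text should be presented as what the achieved size can detect, not as the original justification.

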### Recruitment

Recruitment started 6 months before the starting date of the program via relevant printed information material and health care practitioners (neurologists and nurses) of the Eginition University Hospital Neurological Outpatient Clinic. All study procedures have been discussed face-to-face individually with each potential participant before screening for eligibility by the primary researcher. The primary researcher (ME) has obtained written informed consent from the potential clinical trial participants before the study’s inclusion.

### Assignment of Interventions: Allocation

A block randomization will be conducted after the completion of the first baseline assessment (Figure 1) in equal ratio (1:1:1:1:1:1) to 1 of the 6 study sequences (ABC, BCA, CAB, ACB, BAC, or CBA), as further shown in Table 1 [127]. Concealment is ensured by keeping study material in sealed, opaque envelopes and by using paper assignment. After baseline 1 assessment completion (Figure 1), each participant will be randomized to 1 of the 6 study sequences by the data analyst, and the document with the final groups’ formation will be delivered in a sealed envelope to the principal investigator, who is the responsible for participants’ enrollment.

### Data Collection and Management

All assessments will be conducted face-to-face by an independent investigator to eliminate possible detection bias, except of the Movement Disorder Society-Unified Parkinson’s Disease Rating Scale and Montreal Cognitive Assessment, which will be conducted face-to-face by specialized neurologists of the Eginition University Hospital Neurological Outpatient Clinic.

Participants are free to quit at any time if they wish to discontinue the study. In that case, reasons for withdrawal will be recorded, if this is possible. Participant’s enrollment will be followed by the research team’s assistance during the entire study period, including scheduling of data collection appointments, reminding of intervention’s appointments, and communicating the starting time of each research period.

Data, including consent forms, completed paper-based data files, and study notes, will be securely stored in the main investigator’s office, which will be locked. Raw data will be encrypted and stored digitally on a local computer with access rights to the main investigator. All original data will be archived for 5 years after the completion of the research and then destroyed, according to local regulations. All written data will be stored in a locked cabinet of the main investigator’s locked office for 5 years and then destroyed. Digital data will be stored on a password-protected local computer.

### Statistical Analysis

The primary analysis will evaluate the between group differences in total score of the Greek version of Parkinson’s Disease Questionnaire-8 after each research period. Mean (SD) or summary statistics appropriate to the distribution of the QoL total score will be reported by study group (in-person DfPD vs online DfPD vs control). Study groups will be compared in terms of QoL using mixed model repeated measures considering the correlated data from the same patient [128]. Mixed model repeated measures are robust in small sample size studies; thus, a decreased risk of type II errors occurs [129]. For all secondary end points, summary statistics will be tabulated by study group, and study groups will be compared with a statistical method appropriate to the type of the end point (eg, continuous and categorical end point). Bonferroni correction will be used to account for multiple comparisons of secondary outcomes.

A secondary analysis of the primary end point will adjust for those prerandomization variables which might reasonably be expected to be predictive of favorable QoL total score. Any deviations from the protocol will be recorded and agreed by the investigators. Missing data will not be imputed neither for primary nor secondary analyses, and no interim analyses will be conducted in this study. All the *P* values are 2-sided at an α level of .05. Analyses will be conducted with SPSS (version 20.0; IBM Corp) and R (version 4.4.1; R Foundation for Statistical Computing).

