## Methods

### Study Design

This is a single-centered 3-arm crossover and open-label randomized controlled trial (in-person DfPD vs online DfPD vs control) of UPGRADE-PD (Upbeating Greek Application of Dance in Parkinson’s Disease). Blinding among participants and researchers is not possible due to the nature of the study. There are 6 possible research sequences, as shown in Table 1, and 3 possible carryover effects (1, 2, and 3) for each period from the prior intervention, as shown in Table 2. The study will last 10 months for each participant, including three 2-month research periods and two 2-month washout periods. Assessments will be conducted at enrollment (T_−0_=week −1), baseline periods (T_0_=week 0, T_2_=week 18, and T_4_=week 36), and postinterventional periods (T_1_=week 9, T_3_=week 27, and T_5_=week 45), as shown in Table 3. Allocation to each of the 6 possible sequences will occur after the completion of the first baseline assessment, as shown in the participant flow in Figure 1.

**Table 1 table1:** The UPGRADE-PD (Upbeating Greek Application of Dance in Parkinson’s Disease) study design.

Sequence	Period		
	First	Second	Third
ABC	A^a^	B^b^	C^c^
BCA	B	C	A
CAB	C	A	B
ACB	A	C	B
BAC	B	A	C
CBA	C	B	A

^a^Intervention A (in-person Dance for Parkinson’s Disease combined with usual medical care).

^b^Intervention B (online Dance for Parkinson’s Disease combined with usual medical care).

^c^Control group (usual medical care without Dance for Parkinson’s Disease).

**Table 2 table2:** The UPGRADE-PD (Upbeating Greek Application of Dance in Parkinson’s Disease) study’s code for the possible carryover effect.

Sequence	First period		Second period		Third period	
	Trial	Carryover effect	Trial	Carryover effect	Trial	Carryover effect
ABC	A^a^	0^b^	B^c^	1^d^	C^e^	2^f^
BCA	B	0	C	2	A	3^g^
CAB	C	0	A	3	B	1
ACB	A	0	C	1	B	3
BAC	B	0	A	2	C	1
CBA	C	0	B	3	A	2

^a^Intervention A (in-person Dance for Parkinson’s Disease combined with usual medical care).

^b^Noneffect.

^c^Intervention B (online Dance for Parkinson’s Disease combined with usual medical care).

^d^Effect from intervention A.

^e^Control group (usual medical care without Dance for Parkinson’s Disease).

^f^Effect from intervention B.

^g^Effect from the control group.

**Table 3 table3:** The UPGRADE-PD (Upbeating Greek Application of Dance in Parkinson’s Disease) schedule of enrollment, interventions, and assessments for participants.

Time point (wk)		Study period									

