### Outcomes

#### Primary Outcomes

Patients’ QoL before and after each research period will be assessed by the change in total score of the Greek version [94] of Parkinson’s Disease Questionnaire-8 [95], which is a 0-to-100-point scale with a higher score indicating worse QoL.

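### The primary endpoint is a change in PDQ-8 in one section and an end-of-period PDQ-8 score in another; on the plan's own correlation the two can differ twofold in variance

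*Protocol article*

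**What the plan says.** Under Outcomes, Primary Outcomes, the primary variable is a change score: "QoL before and after each research period will be assessed by the change in total score of the Greek version" of the PDQ-8, a 0 to 100 scale on which higher is worse.

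Under Statistical Analysis, the primary variable reads as the score at the end of the period: "The primary analysis will evaluate the between group differences in total score of the Greek version" of the "Questionnaire-8 after each research period". The word change does not appear there. The method is a mixed model: "Study groups will be compared in terms of QoL using mixed model repeated measures considering the correlated data from the same patient". Neither the response nor the covariates are listed. The only adjustment described is secondary: "A secondary analysis of the primary end point will adjust for those prerandomization variables". Such variables can include the T0 score, but not the scores that open the second and third periods.

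Study Design schedules a baseline before each period, "baseline periods (T_0_=week 0, T_2_=week 18, and T_4_=week 36", and Table 3 shows PDQ-8 at all three as well as at T1, T3 and T5. Sample Size counts six repeated measurements per participant with an average correlation of 0.64.

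**The concern.** A published protocol should fix one primary variable. Here two sections fix different ones, and a separate analysis plan could agree with only one of them. In a crossover the two are not interchangeable. Each participant is already their own control, so subtracting a period baseline may remove noise or add it, depending on how the correlations are arranged.

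Two analysts who each follow one section faithfully would report different estimates and standard errors from the same data, and possibly different conclusions. The trial is open-label, and the analyst who will run the analysis also performs the randomization (Assignment of Interventions). That is a further reason not to leave the choice open until the data are in hand.

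**Working it through.** **Inputs from the article.** Six PDQ-8 measurements per participant, average correlation 0.64, two-sided α 0.05, power 80%, dropout up to 15% (Sample Size, Statistical Analysis); 40 randomized (Results). The PDQ-8 SD is not given, so results are in SD units. The article's sample size of 18 cannot be reproduced, because the effect size behind it is not printed. Only the 0.64 is used here.

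**Assumptions.** Equal variances; correlation *w* between the baseline and end score of the same period; correlation *b* between any two measurements from different periods. Six measurements form 15 pairs, 3 within a period and 12 between, so the average is (3*w* + 12*b*)/15. The article gives only this average; any split is an assumption.

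**Formulas**, per pairwise within-participant contrast, in units of SD²/n:
- End-of-period score: 2(1 − *b*)
- Change score: 4(1 − *w*)
- End-of-period score adjusted for the same-period baseline: 2(1 − *b*)(1 − *r*²), with *r* = (*w* − *b*)/(1 − *b*)

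**Case 1, all correlations 0.64.**
- End-of-period score: 2 × 0.36 = 0.72
- Change: 4 × 0.36 = 1.44
- Adjusted: *r* = 0, so 0.72

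**Case 2, *w* = 0.80 and *b* = 0.60.** The average is (2.40 + 7.20)/15 = 0.64.
- End-of-period score: 2 × 0.40 = 0.80
- Change: 4 × 0.20 = 0.80
- Adjusted: *r* = 0.20/0.40 = 0.5, so 0.80 × 0.75 = 0.60

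Other splits that keep the average at 0.64:

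| *b* | *w* | End score | Change | Adjusted |
|---|---|---|---|---|
| 0.64 | 0.64 | 0.72 | 1.44 | 0.72 |
| 0.62 | 0.72 | 0.76 | 1.12 | 0.71 |
| 0.60 | 0.80 | 0.80 | 0.80 | 0.60 |
| 0.59 | 0.84 | 0.82 | 0.64 | 0.52 |

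A generalized least-squares calculation for the six-sequence design, using all six measurements, gives 0.72 in case 1 and 0.60 in case 2, the same as the adjusted contrast.

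The ordering is general. Adjusted over end score is 1 − *r*², never above 1. Since 1 − *w* = (1 − *b*)(1 − *r*), adjusted over change is (1 + *r*)/2, also never above 1. Change and end score break even at *w* = (1 + *b*)/2.

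**Effect on power in case 1** (noncentral t, df = 2(n − 1) − 2):

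| | End score or adjusted | Change |
|---|---|---|
| Detectable difference at 80% power, n = 40 | 0.38 SD | 0.54 SD |
| Same, 34 completers (40 × 0.85) | 0.41 SD | 0.59 SD |
| Power at 0.4 SD, n = 40 | 84% | 55% |
| n for 80% power at 0.4 SD | 37 | 72 |

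In case 2 with n = 40, scaling 0.38 SD by the root of the variance ratio gives about 0.40 SD for the end or change score (√(0.80/0.72)) and 0.35 SD with adjustment (√(0.60/0.72)).

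**Agreement of the two estimates.** The covariance of the end-score and change contrasts is 2(1 − *w*). Their correlation is 0.72/√(0.72 × 1.44) = 0.71 in case 1 and 0.40/0.80 = 0.50 in case 2. They can therefore differ noticeably in a single data set.

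**The case against.** **The change score has a merit.** If an effect of the previous period persists equally at the baseline and the end of the next one, the change score cancels it. The end-of-period score does not. Suppose in-person dance carries over by an amount L into the next period. In two of the six sequences (ACB and BAC) that period is control, and no in-person period receives it, so in-person minus control shifts by −2L/6 = −L/3. Baseline adjustment removes only the share *r* of this: none in case 1, half in case 2. The choice is thus a trade of variance against one form of bias. This point stands and is reflected in the fix.

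**The doubling is not certain.** It needs all correlations to be equal. In case 2 the two endpoints tie, and at a higher within-period correlation the change score is the better of the two. This also stands.

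**Stronger readings that the article does not support.**
- A reader might infer that the analysis ignores the period baselines and so doubles the variance. The article is silent on them but does not exclude them, and its count of six measurements includes them. In case 1 leaving them out costs nothing (0.72 against 0.72); the doubling comes from subtracting them. Omission would double the variance only at a within-period correlation of about 0.88 to 0.89, which the article does not give.
- A reader might take the phrase about scores after each period to mean separate parallel comparisons, period by period. The mixed model for correlated data from the same patient speaks against that.
- Unnamed period, sequence or carryover terms may properly sit in the full protocol or analysis plan, so their absence from an article is no fault. The secondary analysis on prerandomization variables can stay.

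**Conclusion.** The contradiction is real and lies within the article: Primary Outcomes says change, Statistical Analysis says score after the period. The choice is consequential. With all correlations at 0.64, the change score has twice the variance of the end-of-period or baseline-adjusted contrast. With 0.80 within and 0.60 between periods, change and end score tie and baseline adjustment lowers the variance by a quarter.

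The sizes rest on equal variances, complete data and the assumed split of the average correlation. The existence of the contradiction rests on none of these. Under these assumptions, adjustment for the same-period baseline is best or tied on variance at every split, which makes it the natural way to settle the matter. It does not follow that either stated endpoint is invalid, or that the trial is underpowered.

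**What to change.** Before the analysis is run, put one definition in both Primary Outcomes and Statistical Analysis. Suggested wording:

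*The primary variable is the PDQ-8 total score at the end of each period (T1, T3, T5). It is analysed in one mixed model pooled over the three periods, with the PDQ-8 score at the start of the same period (T0, T2, T4) as a covariate, entered as the deviation from the participant's mean baseline together with that mean. Treatment contrasts are reported pooled over periods.*

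Other ways of entering the same-period baseline are defensible; what matters is that one is named in advance.

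Add a descriptive check of the washout: tabulate the T2 and T4 baselines by the treatment of the preceding period, using the codes already in Table 2. This covers the weakness noted above, that the model does not fully remove a carryover that persists equally at the baseline and end of a period.

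The cost is a few sentences and one or two extra model parameters. No new data are needed, since PDQ-8 is already scheduled at all six visits. The article places the analysis after the last participant leaves the study, so the change can be dated before it.
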